### Recruitment {15}

To recruit participants, we will conduct information events and distribute information material at Hannover Medical School, particularly in our outpatient clinics, as well as place newspaper articles and online advertisements in the Hannover region. In addition, the main Volkswagen factory in Wolfsburg (Lower Saxony, Germany) will contribute to recruitment of participants. Therefore, we will organize a series of online and print advertisements at the factory premises with support of the occupational health centers and the personnel department, which will also distribute advertisements via email and the company intranet to employees.

## Assignment of interventions: allocation

### Sequence generation {16a}

Permuted block randomization with variable block length stratified by sex (male/female) and BMI (< 30/≥ 30 kg/m^2^) is used to allocate patients in a ratio 1:1:1 to the therapy arms. The randomization code is generated in SAS 9.4 using the RANTBL function as default random-number generator. The seed for the randomization procedure is randomly chosen. The randomization code including seed and algorithm is electronically stored in a separate folder and access is granted only for responsible persons involved in generating the randomization list.

### Concealment mechanism {16b}

The randomization is performed centrally by the Institute for Biostatistics; therapy allocation is conducted via fax randomization—the randomization request can either be sent via email or fax. Clinicians involved in the study only receive the result of the allocation via email after the randomization process has been completed. During the course of the trial, clinicians neither have access to the randomization list nor are they directly or indirectly involved in the randomization process.

### Implementation {16c}

The allocation sequence was generated in SAS 9.4 by an independent statistician within the Institute for Biostatistics. Patients can be enrolled by authorized clinicians who are also allowed to request randomization of the patient. The randomization team on duty within the Institute for Biostatistics is responsible for assigning a therapy to each randomized patient according to a trial-specific standard operation procedure. The allocation of the patient is documented on the randomization form which is signed by the randomization team and sent via fax or email to the pre-determined authorized person who requested the randomization. The randomization process is in line with good clinical practice (GCP) guidelines.

## Assignment of interventions: blinding

### Who will be blinded {17a}

Study physicians, exercise scientist, psychotherapist, outcome assessors, and study participants are not blinded for the allocated intervention.

### Procedure for unblinding if needed {17b}

N/A, due to the nature of the study the interventions are not blinded.

## Data collection and management

### Plans for assessment and collection of outcomes {18a}

The data obtained from the screening are recorded manually and subsequently transferred to an electronic case report form (eCRF). The data are subjected to periodic verification for accuracy through random sampling and continuous monitoring. The primary outcome is completed by the patients themselves as part of the initial examination and then verified through a double-entry process before being transferred to the eCRF.

All other study outcomes are collected via online questionnaires at baseline, at the end of treatment after 3 months, and at follow-up, 3 months after the end of treatment. This system precludes the possibility of missing data, as patients are only permitted to proceed or complete the process if all requisite entries have been made. In the event that the questionnaires are not received within a week, the patients are contacted on a weekly basis via telephone or email to remind them of the necessity to complete the questionnaires. The data obtained from the online questionnaires can be exported and evaluated using an evaluation file. The evaluation file was created and verified in advance. Furthermore, the entire process is subject to continuous monitoring.

### Plans to promote participant retention and complete follow-up {18b}

All efforts are made to keep patients in the trial and to collect complete data, in particular for the primary endpoint, even after a premature therapy and/or trial discontinuation. In case that the questionnaires are not completed, the patients are contacted again via telephone or email to remind them to take part in the follow-up.

### Data management {19}

The primary data collection is performed via two web-based systems. The self-reported variables will be captured in the SoSci-Survey Tool, a web-based system provided by the Hannover Medical School (MHH) for creating online questionnaires, sending participation invitations, and downloading data (e.g., as a CSV file). The responsibility for the data collection and sending of participation invitations in SoSci-Survey lies within the Department of Rehabilitation and Sports (MHH) as well as the safe and correct transfer of the data from SoSci-Survey to the Institute for Biostatistics. A standardized process for validated data transfer is provided by the Institute for Biostatistics. All further data (e.g., demographics, safety data) are collected and filed via the web-based EDC-system secuTrial®. secuTrial® is a browser-based GCP-conform EDC-system by the company interactive system for capturing, storing, and managing patient data in clinical trials, non-interventional trials, and patient registers. The eCRF of the trial is based on a Data Dictionary created collectively by the Institute for Biostatistics, the Department of Rehabilitation and Sports Medicine, and the Department of Psychosomatic Medicine and Psychotherapy of the MHH. The MHH provides the server for secuTrial®. The Institute for Biostatistics is responsible for joining the data from SoSci-Survey and secuTrial®, data export, data storing, as well as off-site monitoring. All available data will be exported as a SAS file from secuTrial® and monitored every quartile. Moreover, all available data from SoSci-Survey will be exported as a csv file and provided every quartile to the Institute for Biostatistics. Responsibility for data quality of the raw data as well as for an adequate digitalization of the data lies within the Department of Rehabilitation and Sports Medicine and the Department of Psychosomatic Medicine and Psychotherapy of the MHH. The Institute for Biostatistics is responsible for calculation and derivation of variables, e.g., scores from questionnaires. For quality assurance, all partners of the trial can be audited by responsible employees of the Institute for Biostatistics. Further information on data management and data quality is detained in a data management agreement in the currently active version.

### Confidentiality {27}

All study data collected will be treated confidentially in accordance with the requirements of the data protection law of the federal state Lower Saxony (Germany) and European Privacy legislation. All investigators and trial staff must comply with these requirements in relation to the processing of personal data, with regard to the collection, storage, processing, and disclosure of personal information. Personal data is not accessible to third parties. All data collected will be evaluated in a pseudonymized form, which means that a code number replaces identification features such as name, date of birth, and address so that an assignment to the participant is only possible via an additional reference list. If the study results are published, the confidentiality of personal data will be maintained. According to German law, recorded medical data will be deleted after the usual retention period has expired (currently 10 years after publication).

The online-based implementation of the intervention is supported by online applications. The online video conversations take place via Medflex (medflex GmbH, Konstanz, Germany), a system for video consultations provided by Hannover Medical School. Medflex will only be used as software for the conversation between participants and investigators; no sensitive data, health data, or confidential documents will be shared. The data recorded with the wearable activity tracker (Garmin Forerunner 55, Olathe, USA) are uploaded to the database of our partner Fitrockr (Fitrockr (c/o Digital Rebels GmbH), Berlin, Germany) via an internet connection to a server located in Germany and provided from there to the study staff. The identification of the study participant will be pseudonymized as a code number. The above-mentioned companies have an existing cooperation agreement with Hannover Medical School and have been assessed for data protection and data security within this framework.

### Plans for collection, laboratory evaluation, and storage of biological specimens for genetic or molecular analysis in this trial/future use {33}

N/A, such evaluations are not planned.

## Statistical methods

### Statistical methods for primary and secondary outcomes {20a}

Primary goal of the trial is to show superiority of the combination therapy (exercise therapy and psychotherapy) regarding fatigue symptoms assessed by the FAS in PCS patients compared to the respective monotherapeutic approach. The trial is considered successful if the FAS score is significantly improved for the combination therapy compared to the single exercise therapy and psychotherapy (two-sided alpha of 0.05). Therefore, the trials aims to show superiority of the combination therapy versus the exercise therapy as well as the psychotherapy. Both comparisons are tested co-primarily with a two-sided significance level of 0.05, i.e., both comparisons must be statistically significant for trial success. The primary estimand of the trial is the FAS score and is characterized as follows:Intervention: psychotherapy, exercise therapy, and combination therapy (psychotherapy and exercise therapy).Population: patients ≥ 18 years with ongoing symptoms (longer than 3 months) after proven COVID-19 infection (PCR or antibody test) and a FAS score ≥ 22.Variable: absolute change from baseline to 3 months (end of intervention).Population-level summary: mean difference in the absolute change from baseline in the FAS score.Intercurrent events: patients who die due to an intercurrent event or prematurely end the therapy (because of an adverse event, insufficient efficacy, or other reason) are included in the primary analysis irrespective of this experience, i.e., intercurrent events are handled by applying the treatment policy strategy. Missing values will be replaced conservatively (i.e., in favor of the null hypothesis) using the last-observation-carried-forward (LOCF) approach.

The null and alternative hypotheses for the primary estimand for the co-primary comparisons of the combined therapy versus the respective monotherapeutic approach are defined as follows with µ = FAS (3 months) minus FAS (baseline):H_10_: µ (FAS-change) Combi = µ (FAS-change) PsychotherapyH_11_: µ (FAS-change) Combi ≠ µ (FAS-change) PsychotherapyH_20_: µ (FAS-change) Combi = µ (FAS-change) Exercise therapyH_21_: µ (FAS-change) Combi ≠ µ (FAS-change) Exercise therapy

In line with the treatment policy strategy regarding intercurrent events, the primary analysis is performed in the intention-to-treat (ITT) population, i.e., patients are analyzed as randomized regardless of the actual received therapy or premature trial termination. The change from baseline to 3 months in the FAS score is analyzed using an analysis of covariance (ANCOVA) model with the change from baseline to 3 months in the FAS score as dependent variable, and therapy group, FAS baseline value, and the stratification factors sex (male/female) and BMI (< 30/≥ 30 kg/m^2^) as independent variables. Superiority of the combination therapy compared to the respective monotherapeutic approach is shown (H_10_ and H_20_ are rejected) if (A) improvement in the FAS scores (estimated by least square means) are higher in the combination therapy group than in both monotherapy groups and (B) the *p* value of the associated *F*-test for both comparisons is < 0.05.

Secondary endpoints are analyzed in line with the primary analysis.

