### Criteria for discontinuing or modifying allocated interventions {11b}

One or more of the following circumstances may lead to premature termination of the study for an individual subject: withdrawal of the subject’s consent, occurrence of an exclusion criterion, therapy discontinuation by the patient (not attending therapy visits or documenting discussed therapy contents), and other circumstances that would to lead to worsening of PCS symptoms if continuing the study. For the benefit and interest of the participant, the investigator can terminate study participation at any time if serious side effects or other unforeseeable circumstances occur that endanger the health of the participant. In this case, the Ethics Committee of Hannover Medical School will be informed.

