### Sample size {14}

The sample size calculation is performed for the primary endpoint change from baseline to 3 months in the PCS fatigue symptoms estimated by the FAS. There is currently no published data available regarding the effect of a 3-month single psychotherapy or physical interventions compared to a combined approach on PCS fatigue-specific symptoms. Thus, the assumptions for the sample size calculation are based on preliminary data from a self-conducted pilot study (exercise therapy) and a trial by Kahlmann et al. (psychotherapy), in which a 3-month mindfulness-based, behavioral therapy in patients with chronic lung disease was investigated [8, 11]. A FAS change from baseline at 3 months of 2.0 (standard deviation (SD) = 5.0) for the physical therapy and 4.5 (SD = 5.8) for the psychotherapy, respectively, is assumed. Due to the fundamentally different therapy approaches, it is assumed that there will be more responders and less drop-outs in the combined therapy group compared to each monotherapeutic approach. Thus, a slightly additive effect of 7.0 with a SD of 5.0 is anticipated for the combination therapy. The sample size calculation is based on the comparison between the psychotherapy and the combined therapy approach since the difference of the FAS change for this comparison is assumed to be smaller than between the exercise and combination therapy. With a two-sided type-I-error of 5%, a power of 80%, a pooled SD of 5.0, and a difference of 2.5 in the FAS-change between psychotherapy and the combination therapy using a *t*-test for two independent samples, a sample size of *n* = 64 patients per group is required. With a Satterthwaite test assuming unequal variances (SD = 5.8 for the psychotherapy, SD = 5.0 for the combination therapy), a super additive effect of 7.2 would be necessary to achieve a power of 79.9% with the same sample size. Despite the co-primary group comparison approach, the power does not need to be increased to 90% because of the distinctly larger effect difference between the exercise therapy and the combination therapy (5.0). For a sample size of *n* = 64 patients per group, the power for this comparison of the single exercise therapy with the combination therapy would be > 99%.

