### Methods in analysis to handle protocol non-adherence and any statistical methods to handle missing data {20c}

The primary analysis will be performed in the ITT population, which is in line with the treatment policy strategy to handle intercurrent events, i.e., patients will be analyzed as randomized regardless of the experience of an intercurrent event. Missing values will be replaced using a conservative LOCF approach. A per-protocol (PP) and a complete-case (CC) analysis will be conducted in line with the primary analysis as sensitivity analyses. Patients who (a) do not prematurely ended the trial (i.e., no withdrawal of informed consent, intolerable adverse events, occurrence of an exclusion criterion, premature therapy end by the patient, and other circumstances that would compromise a patient’s health in case of further trial participation) and (b) have a FAS score at 3 months (end of intervention, visit 2) are included in the PP population. The CC population comprises patients who are (a) included in the PP population, (b) participated in at least 5 out of 6 sessions á 50 min or 10 out of 12 sessions á 25 min, (c) have a FAS score at 3 months (end of intervention, visit 2), and (d) do not show any other compliance violations (e.g., not using the wearables, large time period between planned and performed visit (</> 10 days)).

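### LOCF is called conservative, but under the plan's own assumptions it can favour the combined arm; how far depends on unstated missing-data rates and on how drop-outs fare

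*Protocol article*

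**What the plan says.** The statistical methods section {20a} of the protocol article fixes the handling of missing data in the primary analysis: "Missing values will be replaced conservatively (i.e., in favor of the null hypothesis) using the last-observation-carried-forward (LOCF) approach". Section {20c} repeats it: "Missing values will be replaced using a conservative LOCF approach". The estimand in {20a} uses the treatment policy strategy for intercurrent events, and {20a} analyses secondary endpoints in line with the primary analysis.

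Three other parts of the article bear on the direction of LOCF:

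- **Expected improvement.** Sample size {14} assumes "A FAS change from baseline at 3 months of 2.0 (standard deviation (SD) = 5.0) for the physical therapy and 4.5 (SD = 5.8) for the psychotherapy", and "a slightly additive effect of 7.0 with a SD of 5.0 is anticipated for the combination therapy".
- **Expected drop-out.** In the same section, "it is assumed that there will be more responders and less drop-outs in the combined therapy group compared to each monotherapeutic approach". No rate is given.
- **Assessment times.** Section {18a} describes assessments at baseline, at 3 months and at follow-up 3 months later. Section {20c} labels the 3-month assessment visit 2. No FAS in between is described.

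Section {18b} says that efforts are made to obtain data, above all for the primary endpoint, even after a patient stops therapy or leaves the trial.

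**The concern.** LOCF is conservative only if the imputed values pull the arms together, or pull the combined arm down at least as much as its comparators. Here the last observation is the baseline, so each imputed change is exactly zero. In an arm that improves on average, every zero lowers the mean. If more zeros fall in the monotherapy arms, their means are lowered more, and a difference in favour of the combination can appear where none exists.

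Trial success is decided on this analysis. The label also tells a reader that any error from missing data works against the combination, so a positive result would be trusted more than it deserves. The zeros are moreover treated as observed values, and zero change estimates the treatment-policy outcome only if patients with missing scores really stay at baseline.

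**Working it through.** **1. The plan's own figure.** The inputs are those of {14}: "With a two-sided type-I-error of 5%, a power of 80%, a pooled SD of 5.0, and a difference of 2.5 in the FAS-change". The normal approximation gives n = 2 × (1.960 + 0.842)² × 5.0² / 2.5² = 62.8, so 63. The noncentral t-test gives 64 with a power of 80.1%. This agrees with "a sample size of *n* = 64 patients per group is required". The stated 79.9% (difference 2.7, SDs 5.8 and 5.0) and > 99% (exercise comparison) also reproduce. The sample size is not in dispute.

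**2. Bias under LOCF.** Let d be the proportion of missing 3-month scores in an arm and m the true mean improvement of those patients. Replacing their change by zero lowers the arm mean by d × m. If the true arm means are equal and m is the same in both arms:

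bias in (combined − mono) = m × (d_mono − d_combined)

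With balanced missingness this is zero. With fewer missing scores in the combined arm and m > 0 it favours the combined arm.

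**3. False-success rate, combined versus psychotherapy.** Section {20a} requires a two-sided p < 0.05 and the larger improvement in the combined arm, so the nominal rate per comparison is 2.5%. Assumptions: both true means 4.5, SD 5.0, 65 per arm, and missing rates chosen for illustration. With M = 4.5 and c = (M − d × m)/(1 − d), the mean improvement among patients with a score:

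- variance per arm under LOCF = (1 − d) × SD² + d × (1 − d) × c²
- rate = 1 − Φ(1.96 − bias/SE)

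Worked case, 10% vs 20% missing and m = 4.5 (so c = 4.5):

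- bias = 4.5 × 0.10 = 0.45
- variances: 22.5 + 0.09 × 20.25 = 24.32 and 20 + 0.16 × 20.25 = 23.24
- SE = √(47.56/65) = 0.855
- rate = 1 − Φ(1.96 − 0.526) = 7.6%

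| True mean change of drop-outs | Bias, 10% vs 20% | Rate | Bias, 10% vs 30% | Rate |
|---|---|---|---|---|
| improve by 4.5 | +0.45 | 7.6% | +0.90 | 18.7% |
| improve by 2.0 | +0.20 | 4.2% | +0.40 | 6.7% |
| no change | 0 | 2.5% | 0 | 2.5% |
| worsen by 2.0 | −0.20 | 1.4% | −0.40 | 0.8% |

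For the first row, unadjusted calculation with SD 5.8 for psychotherapy gives 6.8% and 16.5%. Simulation of the baseline-adjusted ANCOVA (assumed baseline SD 6 and slope −0.3; 10,000 runs) gives 8.9% and 20.8%. Hence the ranges of about 7–9% and 16–21%.

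**4. The full both-must-win rule** (simulated, m equal to the arm mean, same missing rate in both monotherapy arms):

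| True means (combined, psychotherapy, exercise) | No missing | 10/20% | 10/30% |
|---|---|---|---|
| 4.5, 4.5, 2.0 | 2.2% | 8.7% | 21.2% |
| 4.5, 4.5, 4.5 | 0.4% | 2.7% | 9.3% |

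Where exercise is clearly weaker, as {14} assumes, the second comparison gives almost no protection. In the first row, analysing only observed scores at 10/30% gives 2.4% with no bias.

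**5. The planned alternative (7.0 vs 4.5).** The expected difference under LOCF is 7.0 × (1 − d_combined) − 4.5 × (1 − d_mono). It exceeds 2.5 once d_mono/d_combined is above 7.0/4.5 = 1.56. At 10/20% it is 6.30 − 3.60 = 2.70; at 10/15% it is 6.30 − 3.825 = 2.475; at 10/10% it is 2.25. Thus LOCF attenuates the planned effect when missingness is near balance and enlarges it when the imbalance is larger.

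**The case against.** The strongest counter-argument is that the plan never says how many 3-month scores will be missing. The drop-out statement in {14} supports the assumed effect of 7.0; it is not a forecast of missing FAS. Section {18b} seeks the primary endpoint after discontinuation and {18a} adds weekly reminders, so the rates of missing scores may be well below those of therapy drop-out. This stands, and it is why the size can only be a range.

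Second, the inflation needs drop-outs who would have improved. The plan's reasons for stopping include insufficient efficacy, adverse events and, in {11b}, "other circumstances that would to lead to worsening of PCS symptoms if continuing the study". If such patients stay at baseline, LOCF is unbiased; if they worsen, scoring them as unchanged is conservative as long as more of them are in the monotherapy arms. This also stands. It shows that the direction depends on behaviour that cannot be observed, which is not what the label says.

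Third, {14} ties fewer drop-outs to a larger combined effect, so attaching the imbalance to a null of equal means combines two scenarios. That is fair as to likelihood. Yet false-success rates must be judged under the null, and nothing in the plan makes drop-out balanced there.

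Fourth, {20c} plans per-protocol and complete-case analyses, which might reveal a result driven by LOCF. They do not repair it. Success rests on the LOCF analysis, the per-protocol set excludes everyone who ended prematurely, and the complete-case set is nested within it. Neither keeps the ITT population under another missing-data assumption.

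A reader might infer that the primary test definitely fails its 5% level, or that LOCF always favours the combination. The documents do not support that: they give no rates and no outcome for drop-outs, and the table above contains neutral and conservative cases.

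**Conclusion.** The description of LOCF as conservative is unsupported as written and can be reversed by the plan's own assumptions: improvement in every arm, fewer drop-outs in the combined arm, and no described FAS between baseline and 3 months. The size is conditional. At assumed missing rates of 10/20% to 10/30%, the false-success rate against psychotherapy runs from about 1% (drop-outs worsen by 2 points), through 2.5% (no change) and about 4–7% (improve by 2.0), to about 7–21% (improve by 4.5). If all three arms are equal, the rate for the whole trial is about 3% to 9%, against 0.4% without drop-out.

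This rests on three assumptions: the drop-out imbalance carries over to missing scores after the efforts in {18b}; the chosen rates; and no interim FAS in Table 1, which is not shown. The schedule sentence in {18a} strictly concerns the other outcomes, but the visit 2 label in {20c} makes an interim FAS unlikely. The point is not an omission that an analysis plan could fill, because the protocol fixes the method and states its direction.

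**What to change.** 1. In {20a}, delete the words that describe the replacement as conservative and in favour of the null; in {20c}, delete the word conservative.
2. Make multiple imputation by arm the missing-data method of the primary ITT analysis, with the same ANCOVA contrasts. Include baseline FAS, sex, BMI, the other fatigue scales, the 6-month FAS where available, and discontinuation status with post-discontinuation FAS where collected. The last item matters: imputation that only makes missing patients resemble completers would not match the treatment-policy estimand either.
3. Add a delta-adjusted or tipping-point sensitivity analysis that penalises missing scores in the combined arm.
4. Keep LOCF only as a labelled sensitivity analysis, and carry the change over to the secondary endpoints.

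The cost is a change of wording, modest programming and somewhat wider confidence intervals than under LOCF. No new data are needed.

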**Methods:**

The study will be conducted as a prospective, randomized controlled, open-label trial with 3 treatment arms (exercise therapy, psychotherapy, and combined therapy). According to the sample size calculation, 65 participants will be enrolled in each group. The primary outcome is the change of PCS fatigue symptoms from baseline to 3 months, estimated by the Fatigue Assessment Scale. Secondary endpoints include changes in further measures of fatigue (Chalder Fatigue Skala, Multidimensional Fatigue Inventory, Post-exertional Malaise Scale, Bell Scale), health-related quality of life (Short Form-36 and Brief Illness Perception Questionnaire), anxiety and depression (Hospital Anxiety and Depression Scale), and work ability (Work Ability Index). The intervention lasts for 3 months and includes online therapy sessions of 50 min every 2 weeks or in case of lack of concentration or fatigue this could be split to two 25-min sessions (all equating to a total of 300 min of specialist care). The psychotherapy adopts a short-term and coping-oriented approach based on the unique requirements of each patient from a psychotherapeutic perspective. Exercise therapy involves a personalized physical activity plan customized to suit the patient’s requirements, with tracking day-to-day physical activity along with daily moderate endurance and strengthening workouts. An ANCOVA model, including the stratification factors sex and BMI, will be used for the primary analysis of Fatigue Assessment Scale. Significance tests will be based on the group differences in least square means and corresponding 95% CIs.

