### Intervention description {11a}

The study consists of three arms, each including 300 min of online therapy sessions over a period of 3 months, and a follow-up period of 3 months (6 months after BSL). The therapy consists of 300-min online intervention with 50-min sessions every 2 weeks (alternatively up to 12 × 25 min every week). The interventions are led by an exercise scientist and a psychological psychotherapist, respectively.

In the exercise therapy intervention, an individual exercise plan will be developed during the first online session based on the results of the aptitude test and the participant’s descriptions and routines. This exercise plan includes managing daily activities, a heart rate limit, moderate endurance and strength exercises, as well as stretching and relaxation exercises. To account for the physical inactivity caused by fatigue in many participants, light strengthening exercises (e.g., chair squats and wall push-ups) and shorter endurance exercises (e.g., walking, ergometer training, Nordic walking, cycling) will be usually performed at the beginning. If participants are currently receiving therapy, such as regular physiotherapy or ergotherapy, this will be integrated into the exercise plan and planned around it. The exercise plan aims to increase the frequency of strength and endurance training stimuli and to adjust the intensity to individual circumstances without causing overload or crashes. The activities are recorded using a wearable device. To ensure subjectivity of the intensities, the patients will keep a training diary during the intervention, in which the subjective feeling of exertion is assessed using the Borg scale and the daily feeling in the morning and in the evening (scale 1–10) is documented. During therapy sessions, activities will be discussed and exercise plans and the time between sessions will be considered. This includes wearable data, training diaries, sleep patterns, recovery, and existing therapies such as physiotherapy and occupational therapy. Other strenuous activities, such as cognitive activities, will also be taken into consideration as well as the physiology of training, fatigue, and recovery. The exercise therapy aims to improve reduced resilience and fatigue without overwhelming patients with volume or intensity. This will be achieved through a comprehensive approach that allows patients to engage in continuous, daily physical activity.

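### Secondary endpoints inherit last-observation-carried-forward from the 3-month primary analysis; at the 6-month follow-up that rule carries the end-of-therapy score and is not assured to be conservative

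*Protocol article*

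**What the plan says.** The section on statistical methods {20a} sets the primary variable as the FAS change to the end of the intervention: "Variable: absolute change from baseline to 3 months (end of intervention". Its missing-data rule reads: "Missing values will be replaced conservatively (i.e., in favor of the null hypothesis) using the last-observation-carried-forward (LOCF) approach". The section on non-adherence and missing data {20c} repeats it without naming an endpoint or a visit: "Missing values will be replaced using a conservative LOCF approach".

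For everything else, {20a} gives one sentence: "Secondary endpoints are analyzed in line with the primary analysis". No separate missing-data rule for secondary endpoints follows.

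The section on outcome collection {18a} says that outcomes other than the primary are collected by online questionnaire at baseline, "at the end of treatment after 3 months, and at follow-up, 3 months after the end of treatment". The intervention description {11a} likewise gives every arm "a follow-up period of 3 months (6 months after BSL", that is, after baseline). The abstract describes the secondary endpoints only as changes ("Secondary endpoints include changes in further measures of fatigue" and in other scales) and gives no time point.

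**The concern.** The claim that LOCF favours the null was written for an endpoint at 3 months. The only earlier FAS value described is baseline, so carrying it forward records no change.

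At 6 months the last available value is normally the 3-month score, taken at the end of therapy. A patient who improved, relapsed during the three months without therapy and did not return the last questionnaire would be analysed as having kept the improvement. The rule then builds persistence into the data for the period in which persistence is unknown. At stake are the size of maintained improvement in each arm and the 6-month comparisons between arms.

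Missing 6-month questionnaires are possible. The online form blocks skipped items, but {18a} and {18b} plan reminders for questionnaires that are not returned.

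The named sensitivity analyses would not clearly expose the problem. In {20c} both the per-protocol and the complete-case set are defined by a FAS score at 3 months, and neither explicitly requires a 6-month score. A patient who completed therapy and then fell silent could be in both sets with a carried value.

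**Working it through.** **Planning figures reproduced.** The sample size section {14} states: "With a two-sided type-I-error of 5%, a power of 80%, a pooled SD of 5.0, and a difference of 2.5 in the FAS-change". An exact two-sample t-test gives 63.8, so 64 per group, with power 80.1%; the normal approximation gives 63. The Welch variant (SD 5.8 and 5.0, difference 7.2 − 4.5 = 2.7, n = 64) gives 79.9%, as stated. Combination versus exercise (difference 5.0) gives more than 99.9%, consistent with the stated figure above 99%. The planning inputs can therefore be used for illustration.

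**Inputs from {14}.** Improvement at 3 months (m3): exercise 2.0, psychotherapy 4.5, combination 7.0 FAS points. SD 5.0, 65 per arm.

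**Assumptions (the documents give no values).** d is the share of an arm with a 3-month but no 6-month score, missing independently of the scores; r is the fraction of benefit retained at 6 months. Patients missing both visits carry baseline and do not enter d. FAS planning values stand in for the secondary scales, which have none.

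**Within an arm.** Expected 6-month improvement under LOCF = m3 × [r(1 − d) + d]. The truth is m3 × r, so the bias is m3 × (1 − r) × d.

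| Combination arm | truth | d = 10% | d = 20% | d = 30% |
|---|---|---|---|---|
| full relapse, r = 0 | 0 | 0.70 | 1.40 | 2.10 |
| half retained, r = 0.5 | 3.50 | 3.85 | 4.20 | 4.55 |
| fully retained, r = 1 | 7.00 | 7.00 | 7.00 | 7.00 |

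**Between arms, equal missingness m.** LOCF estimates (1 − m) × D6 + m × D3, where D3 and D6 are the true differences at 3 and 6 months. Bias = m × (D3 − D6). With D6 = 0:

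- versus psychotherapy (D3 = 2.5): 0.25 / 0.50 / 0.75 points at 10 / 20 / 30%;
- versus exercise (D3 = 5.0): 0.5 / 1.0 / 1.5 points.

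If half the difference is retained, these biases halve.

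**Rejection rate.** Standard error = 5.0 × √(2/65) = 0.877. Noncentrality is the bias divided by 0.877: 0.29 / 0.57 / 0.86 versus psychotherapy and 0.57 / 1.14 / 1.71 versus exercise. The two-sided 5% t-test with 128 degrees of freedom then rejects in 5.9 / 8.7 / 13.6% and 8.7 / 20.5 / 39.7% of trials.

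Holding the SD at 5.0 ignores the spread added by mixing carried and observed scores. That adds d(1 − d) × m3² to each arm's variance. At d = 30% the combination arm has 25 + 0.21 × 49 = 35.3, psychotherapy 25 + 0.21 × 20.25 = 29.3 and exercise 25 + 0.21 × 4 = 25.8. The standard errors become √(64.5/65) = 1.00 and √(61.1/65) = 0.97, and rejection at 30% falls to about 12% and 34%. The pattern is unchanged.

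**Between arms, unequal missingness, full relapse.** Bias = 7.0 × d(combination) − m3(monotherapy) × d(monotherapy). With 5% in the combination arm and 20% in the others:

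- versus psychotherapy: 0.35 − 0.90 = −0.55;
- versus exercise: 0.35 − 0.40 = −0.05.

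Both are against the combination. The sign turns when monotherapy missingness exceeds 7.0/4.5 = 1.56 times (psychotherapy) or 7.0/2.0 = 3.5 times (exercise) that of the combination arm.

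**The case against.** The strongest reply is that no 6-month endpoint is defined. The only analysed variable with a time point is the 3-month FAS change. Analysing secondary endpoints in the same way could mean the same model on the same 3-month change, in which case baseline is carried and the problem does not arise. Both LOCF sentences stand next to text on the primary analysis. This stands to the extent that the 6-month analysis is inferred from the visit schedule. Even so, the article states a rule for all secondary endpoints, does not limit it by visit, and has the outcomes collected at 6 months. That is a stated rule that reaches too far, not merely a detail left to the analysis plan.

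A reader might go further and infer that LOCF at 6 months is the reverse of conservative and favours the combination whenever there was a 3-month difference. The documents do not support that. The bias needs a shrinking difference, is zero if the difference persists, and goes the other way if the difference grows or the combination arm has clearly less missingness. Section {14} does expect fewer drop-outs under combination therapy. It gives no rate, however, and speaks in the context of the 3-month endpoint. Patients lost before 3 months carry baseline and do not enter d, so unequal 6-month missingness is not established either.

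It is also fair that the illustrated rates assume complete loss of the difference, that missingness of 10 to 30% is not a protocol figure, that durability is not a stated objective, and that trial success rests on the 3-month FAS alone.

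**Conclusion.** The concern holds in a limited form. For any 6-month analysis under the inherited rule, LOCF is not assured to be conservative.

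Within an arm it overstates maintained improvement whenever benefit fades, whatever the balance of drop-out: by 1.4 FAS points in the combination arm at 20% missing and full relapse, and by 0.7 if half the benefit is retained. Between arms the direction is not fixed. On the assumptions shown, the bias versus psychotherapy runs from +0.75 points (30% missing in both arms) to −0.55 (5% versus 20%). With equal missingness of 10 to 30%, full loss of the difference and SD 5.0, false rejection rises from 5% to about 6–14% versus psychotherapy and 9–40% versus exercise.

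The point does not touch the primary analysis, the criterion for trial success or the sample size. It is a change worth making, not a threat to the main conclusion.

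**What to change.** In {20a} and {20c}, state the time points of the secondary endpoints, and limit LOCF and the word conservative to the 3-month analysis.

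Analyse 6-month secondary outcomes with a mixed model for repeated measures on the changes at 3 and 6 months (therapy, visit, therapy-by-visit, the scale's own baseline, sex, BMI group), or with multiple imputation. Optionally add a sensitivity analysis in which missing 6-month scores return to baseline.

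The cost is wording and a standard model run on data already being collected, with no new patients or visits. Intervals at 6 months may be slightly wider and the results possibly less favourable.
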